### Process measures

We will use the RE-AIM Framework as our basis to evaluate SCALA’s impact across the five dimensions of reach, efficacy, adoption, implementation, and maintenance
^138–
140^, ensuring fidelity in its completion
^141^,
Figure 4.

**Figure 4. f4:**
[figure not shown]
RE-AIM dimension and SCALA aims, activities and main outcome/process measures. PHCU, primary health care unit; PHC, primary health care; AUD, alcohol use disorder.

At least four elements will be included. First, a driver diagram
^142^ will be used to identify drivers for successful scale-up. To enable a nuanced understanding of how scale-up varies in the different cities, recognizing that context can have a greater influence on scale-up than any pre-specified implementation strategy, the driver diagrams will provide real- time continuous feedback on how changing contexts in health systems or city actions affect outcomes. Second, the evaluation procedure of WHO’s Urban Health Equity Assessment and Response Tool (Urban HEART)
^143^ will be modified to identify the barriers and facilitators to scale-up. Third, the factors influencing the progress from scale-up to outcomes will be identified and documented based on UK Medical Research Council guidance
^144^ analysing factors within five groups: (i) description of intervention and its causal assumptions; (ii) context; (iii) implementation; (iv) mechanisms of impact; and, (v) outcomes. Fourth, using the detailed methodology of Ysa
*et al.*
^145^, the experience and outcomes of the scale-up will be mapped with contextual, financial and political-economy analyses of the cities and the countries within which they are located. The following contextual factors will be collected: (1) available data similar to that of the OECD better life initiative
^146^, including material living conditions (housing, income and jobs) and quality of life (community, education, environment, governance, health, life satisfaction, safety and work-life balance); (2) Sustainable Governance Indicators
^147^, including the Status Index, which ‘examines each state’s reform needs in terms of the quality of democracy and performance in key policy fields’, and the Management Index, focused on ‘governance capacities in terms of steering capability and accountability’; and, (3) World Values Survey data
^148,
149^ for cross-cultural variation (Traditional vs. Secular-rational; and, Survival vs. Self-expression). Documentation will be complied either at municipal or country level for alcohol policy-related strategies, action plans, legislation and evaluations. A model will be built on two levels of analyses, contextual factors and policy factors and this will be mapped on to the test of the scale-up of the PHC interventions to describe and identify those contextual and policy factors that might influence going to full-scale beyond the implementation cities.

### Sample size

Our power calculations are based on the following assumptions: at baseline, 2.5/1,000 consulting patients will be found to be screen positive (based on an AUDIT-C cut-off score of 8) and advised to reduce their alcohol consumption (data from ODHIN study; [name], personal communication). To detect an increase in the number to 5/1,000 (a doubling), with 80% power and a significance level of 5%, and assuming a design effect of ten PHCUs per three cities per group (scale-up and comparator), with an ICC for PHCUs across countries = 0.03 (data from ODHIN study; [name], personal communication), a conservative estimate of 30 PHCUs across three scale-up cities and 30 across three comparator cities, about ten per city will be needed
^150^, assuming an average PHCU size of about 8,000 patients with a monthly consultation rate of 1,200 adult patients per PHCU (data from ODHIN study; [name], personal communication).

### Statistical measures

The primary outcome of the study will be the proportion of consulting adult patients intervened (screened and advice given to screen positives) measured during two four-week periods midway and at the end of the 18-month scale-up period, and this will be analysed at the levels of the PHCU and provider by city type (intervention or control)
^151^. Given the rarity of the event and the resulting distribution, we will use exact inference methods for comparison of intervention vs. control cities. For further analyses, including covariates, regression models will be used, taking into consideration the hierarchical nature of the data
^152^, and characteristics at different hierarchy levels (i.e., characteristics of the PHCU, characteristics at the city level, such as patterns of drinking), and incorporating 4-week baseline period measurements as covariates. Special consideration will be given to the skewness of data by applying models, such as zero-inflated binomial regression, after testing for necessary assumptions
^153,
154^. Odds ratios will be presented with 95% confidence intervals. For any PHCU or provider that drops out during the study, outcome values for subsequent measurement points will be set at the last value obtained.

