## Abstract

**Background**: While primary health care (PHC)-based prevention and management of heavy drinking is clinically effective and cost-effective, it remains poorly implemented in routine practice. Systematic reviews and multi-country studies have demonstrated the ability of training and support programmes to increase PHC-based screening and brief advice activity to reduce heavy drinking. However, gains have been only modest and short term at best. WHO studies have concluded that a more effective uptake could be achieved by embedding PHC activity within broader community and municipal support.

**Protocol**: A quasi-experimental study will compare PHC-based prevention and management of heavy drinking in three intervention cities from Colombia, Mexico and Peru with three comparator cities from the same countries. In the implementation cities, primary health care units (PHCUs) will receive training embedded within ongoing supportive municipal action over an 18-month implementation period. In the comparator cities, practice as usual will continue at both municipal and PHCU levels. The primary outcome will be the proportion of consulting adult patients intervened with (screened and advice given to screen positives). The study is powered to detect a doubling of the outcome measure from an estimated 2.5/1,000 patients at baseline. Formal evaluation points will be at baseline, mid-point and end-point of the 18-month implementation period. We will present the ratio (plus 95% confidence interval) of the proportion of patients receiving intervention in the implementation cities with the proportions in the comparator cities. Full process evaluation will be undertaken, coupled with an analysis of potential contextual, financial and political-economy influencing factors.

**Discussion**: This multi-country study will test the extent to which embedding PHC-based prevention and management of alcohol use disorder with supportive municipal action leads to improved scale-up of more patients with heavy drinking receiving appropriate advice and treatment.

**Study status**: The four-year study will start on 1
^st^ December 2017.

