### Cities

Intervention municipalities that have confirmed technical and political consent to be involved have been investigator-selected from Bogotá (Colombia), Mexico City (Mexico) and Lima (Peru). Comparator municipalities have been investigator-selected in Bogotá, Mexico City and Lima, on the basis of comparability with the scale-up municipality in terms of socio-economic and other characteristics which impact on drinking, health care and survival, comparable community mental health services, and sufficient geographical separation to minimize spillover effects from the intervention municipality. Randomized selection of the municipalities was excluded as the hypotheses and the study approach relies on municipal-level interventions. Cities are chosen as the scalable unit, as there is a systemic global trend for municipalities to increasingly take on the jurisdictional responsibilities for prevention and health care services. Cities, themselves, are active in prevention and health promotion programmes, and there is a strong evidence base for their impact, also in the prevention of alcohol-related harm
^85,
86^. Cities are a natural site for preventing alcohol-related harm
^87^. Although not having the full jurisdictional responsibilities of national governments for all alcohol policy issues, they often have greater flexibility and are an important site for both media-based and social norms programmes, as well as environmental measures to manage and limit availability of alcohol
^88^. Networks of cities are natural vehicles for exploitation of the results and deployment to full scale, more so with the trends of increasing urbanization in Latin America
^89,
90^.

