### Participants

Approximately ten PHCUs per intervention and comparator cities will be involved, 60 PHCUs in total. The exact number of PHCUs will depend on the average number of registered patients per PHCU. In each city, the total number of recruited PHCUs should cover a population of about 80,000 registered patients (including children and adults). In jurisdictions, where PHC physicians work as individual practitioners, a PHCU can be defined for the purposes of the study as a virtual or physical location where three or more PHC physicians work. Identification of PHCUs who agree to participate in the studies will be drawn from administrative or academic registries of PHCUs at national, regional, or city levels. The process of recruiting PHCU will be described in detail by each country. Within each PHCU, eligible providers will include any fully trained medical practitioner, nurse or practice assistant with a non-temporary employment contract, working in the PHCU and involved in medical and/or preventive care. These providers will sign an informed consent for their participation. Dependent on customary country practice, participating PHCUs will receive a study fee.

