### Tailoring PHC screening and advice package

SCALA is a trans-cultural study, with different health systems, and differences in drinking patterns and attendance at PHC centres, compounded by gender differences. In Mexico, for example, men consume more alcohol then women, but attend PHC services much less frequently than women
^53^. Thus, there is a need for careful tailoring of the screening and advice package. Each intervention city will create Community Advisory Boards (CABs) representing academia, city health and public health departments, health service commissioners and practitioners, and patient and public engagement groups; and User Panels (UPs) of user groups, including PHC providers, patients and citizens. Through expert meetings, workshops, and focus groups, the package will be fine-tuned and tailored to the needs of each city, based on the Tailored Implementation for Chronic Diseases initiative
^100–
102^ within the seven domains of: local and national guideline factors; individual health care provider factors; patient factors; interactions between different professional groups; incentives and resources; capacity for organizational change; and, social, political and legal factors. At the city level, tailoring will be based on the principles of integration between PHC and municipal services
^103^ and the development of complementary community ecosystems that support reductions in heavy drinking. At the PHC level, tailoring will be based on the principles of co-production of health
^104^ between PHC providers and patients.

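### The design is three within-country city pairs, but the primary exact comparison is defined by city type alone, with no country or pair stratum

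*Protocol article*

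**What the plan says.** The Cities section describes matched selection: "Comparator municipalities have been investigator-selected in Bogotá, Mexico City and Lima, on the basis of comparability with the scale-up municipality". Each country therefore supplies one intervention and one comparator municipality, both in the same capital.

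Statistical measures places the primary analysis at PHCU and provider level, by city type (intervention or control). Because the event is rare, "we will use exact inference methods for comparison of intervention vs. control cities". The exact method is not named, and neither country nor pair is mentioned. Hierarchy, PHCU and city characteristics and the baseline measurement enter in a separate sentence about further analyses by regression. The Abstract promises a ratio of "the proportion of patients receiving intervention in the implementation cities with the proportions in the comparator cities", again without reference to country.

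On allocation, Participants plans about ten PHCUs per city, and adds: "The exact number of PHCUs will depend on the average number of registered patients per PHCU". It then sets a target of about 80,000 registered patients, children included, in every city. Under Outcomes, the primary denominator is the number of adult consultations of the participating providers.

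On differences between countries, the tailoring section describes a study "with different health systems, and differences in drinking patterns and attendance at PHC centres". The Introduction gives heavy episodic drinking of 4, 11 and 12% and alcohol use disorder of 6, 7 and 3% for Colombia, Mexico and Peru.

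**The concern.** The design pays for within-country matching, but the stated primary contrast does not use it. Without a country stratum, the null is that all intervention units and all control units come from the same mixture. That matches no effect within any country only if the three countries have the same rate, or if each country contributes the same share of units to both arms.

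Two things are at stake. If shares are equal, between-country variation stays in the null distribution and the test is less sensitive than the design allows. If shares differ and country rates differ, the crude ratio departs from 1 with no effect anywhere, and a test of it can reject too often. This is confounding by country. It is separate from clustering within PHCUs and would remain if the ICC were zero.

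**Working it through.** **Inputs from the protocol.** Baseline 2.5 per 1,000, target 5 per 1,000, 80% power, 5% level, ICC 0.03, 1,200 adult consultations per PHCU per month, 30 PHCUs per group (Sample size); about 10 PHCUs per city (Participants); drinking prevalences 4, 11, 12% (Introduction).

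**The plan's own figure.** The usual two-proportion formula (two-sided 5%, 80% power) for 0.0025 against 0.005 gives 9,383 consultations per group, or 9,383/1,200 = 7.8 PHCUs. With design effect 1 + (1,200 − 1) × 0.03 = 36.97 this becomes about 289 PHCUs, so 30 per group is not reproduced. That is a separate matter. It matters here only because power at ICC 0.03 is low with or without strata.

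**Assumptions not in the protocol.** Outcome rates proportional to 4:11:12 with mean 2.5 per 1,000: 7.5 × 4/27 = 1.11, 7.5 × 11/27 = 3.06 and 7.5 × 12/27 = 3.33 per 1,000. Paired cities share one true rate when there is no effect. An ICC of 0.0016 serves as the low alternative: a PHCU coefficient of variation of 0.8 gives 0.64 × 0.0025/0.9975 = 0.0016.

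**Step 1: planned allocation, 10/10/10 in both arms.** The country mixes are equal, so the crude ratio with no effect is 1. Simulated PHCU-level rank tests, unstratified against stratified by country:

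| Quantity | Unstratified | Stratified |
|---|---|---|
| Power for a doubling, ICC 0.0016 | 0.85 | 0.91 |
| Power for a doubling, ICC 0.03 | 0.30 | 0.32 |

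The unstratified type I error is 0.01–0.05, so the test is conservative. With steeper assumed country rates the power loss is larger: 0.77 against 0.89 for 1:2:4 and 0.60 against 0.95 for 1:3:9 at ICC 0.002; 0.31 against 0.35 and 0.30 against 0.43 at ICC 0.03.

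**Step 2: unequal PHCU numbers.** Take 7/10/13 intervention against 13/10/7 control PHCUs, no effect, equal consultations per PHCU:

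- Intervention rate: (7 × 1.11 + 10 × 3.06 + 13 × 3.33)/30 = 2.72 per 1,000.
- Control rate: (13 × 1.11 + 10 × 3.06 + 7 × 3.33)/30 = 2.28 per 1,000.
- Crude ratio: 2.72/2.28 = 1.19, although every within-country ratio is 1.

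The unstratified PHCU-level test then rejects in about 6–11% of runs, with the low end at the stated ICC of 0.03. At the milder 8/10/12 against 12/10/8 it rejects in at most 6.7%, even with country rates 1:2:4 or 1:3:9. The stratified test stays at 4–7% throughout.

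**Step 3: other units of analysis.**

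- *Consultation level*, no clustering, 36,000 consultations per arm in one window. Country volumes of 9/12/15 against 15/12/9 thousand give 2.685/2.315 = 1.16. Expected events are 36 × 2.685 = 96.7 and 36 × 2.315 = 83.3, so z = 13.4/√180 ≈ 1.0. Rejection is about 17% by normal approximation and 15% by simulation of the exact test. Volumes of 10/12/14 against 14/12/10 give a ratio of 1.10 and 8%; 8/12/16 against 16/12/8 give 1.22 and 24%.
- *Provider level*, 3/4/5 against 5/4/3 providers per PHCU, no clustering, country rates 1:2:4 or 1:3:9: rejection of 0.26 and 0.61, against 0.03 and 0.01 when provider numbers are equal.

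**The case against.** A reader might infer that the protocol commits to a pooled test that falsely rejects when there is no effect. The document does not support that. It names the contrast but no method. Stratified conditional tests and within-stratum permutation are exact methods too, and the detail may sit in an analysis plan that is not shown. The rule on PHCU numbers, read with the sentence after it, is a balancing rule: numbers vary so that each city covers about the same registered population. At that balance the unstratified PHCU-level test is conservative. The large consultation-level rejection rates need a test without clustering and mirror-image imbalances aligned with country rates. Tying the outcome to drinking prevalence is also an assumption, since the outcome measures provider activity. All of this stands and limits the point.

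Two further defences hold only in part. The regression models allow for hierarchy and city-level drinking patterns, and the Discussion mentions propensity score matching, but neither is tied to the primary exact comparison. The balancing target counts registered patients of all ages, whereas the denominator counts adult consultations of participating providers, whose number is not set. Equal shares are intended but not secured.

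A reader might also infer that stratifying makes the test valid. It does not. With an assumed between-city SD of 0.2–0.5 on the log rate, the stratified test's type I error is 0.10–0.27. A sign-flip test on three pairs cannot give a two-sided p below 2/2³ = 0.25.

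**Conclusion.** The point holds as a mismatch between a design paired by country and a primary comparison defined by city type alone. It goes beyond missing detail, because the protocol states the comparison factor and assigns structural adjustment to other analyses.

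At the planned allocation the cost is some power: about 6 percentage points at an assumed ICC of 0.0016 and about 2 at the stated 0.03, with rates proportional to the heavy-episodic-drinking figures. Inflation above 5% is conditional. It needs country rates that differ and a realised country mix that differs between arms. At PHCU level it is about 6–11% under the fairly strong 7/10/13 imbalance; it is larger if providers or consultations are the unit. If the countries have equal rates or contribute equal shares, there is no inflation. The country rates, the imbalance patterns and the low ICC are assumptions, not protocol figures.

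**What to change.** In Statistical measures, name the exact method and its unit, and state that the primary comparison is stratified by country pair: rank or permute within country only, or use a stratified conditional exact method. Include country as a fixed effect in the regression models. Report the three country-specific ratios beside a country-stratified combined ratio, and let the latter replace the crude pooled ratio suggested by the Abstract.

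The cost is one or two sentences, no new data, and two degrees of freedom for country, with negligible loss of precision if the countries turn out alike. The text should add that this removes only the error due to country mix. Clustering within PHCUs and providers, and city-level variation across three non-randomised pairs, need separate treatment.

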## Protocol

### Design

The study is a quasi-experimental design
^84^, comparing changes in screening and brief advice, and, if relevant, referral for treatment activity, amongst primary health care units (PHCUs) in intervention cities with PHCUs in similar control cities,
Figure 2.

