^144^, developing logic models to document the fidelity of all implementation strategies, and to identify, the drivers and barriers and facilitators to successful implementation and scale-up, and the political and economic contextual factors that might influence scale-up, based on the RE-AIM framework
^138^.

And, finally, tenth, we place the study design in the public domain, so that others might replicate the study approach (with acknowledgment) to see if the scale-up principles can work across jurisdictions. In so doing, we would be pleased to receive comment and feedback.

We are aware of some limitations of the study design. As we are unable to randomize the involved cities, we adopt a quasi-experimental design, recognizing that it is not possible to randomly allocate the municipalities. Randomized selection of the municipalities was excluded as the hypotheses and the study approach relies on municipal-level interventions. A trial with random assignments of municipalities is not feasible due to cost (number of municipalities) and municipal-based political and technical considerations. Randomization of primary health care centers within municipalities is also impossible for the same reasons of municipal involvement in the interventions. Clean control conditions in this environment where the municipality supports primary health care-based does not seem to be possible. As a result, we created a quasi-experimental design
^84,
160,
161^, trying to optimize control for confounding, and using propensity score matching (PSM), given the above constraints. While full control via randomization, and thus establishment of causality is not possible, together with the qualitative evaluation component of the study, we will be able to clearly identify the mechanisms which were crucial in leading to the outcomes. According to a recent 7-item checklist for classifying quasi-experimental studies for Cochrane reviews
^162^, our approach is, nevertheless, ranked as a strong design.

Although our focus on embedding PHC activity within supportive municipal actions is hypothesized to increase screening and brief activity over and above that previously demonstrated, such an approach also brings risks. Municipal governments change; and, thus health priorities may change. Although our approach minimizes the need for extra resources (and in some jurisdictions, could be resource saving
^34,

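### The design promises a comparison of changes, but the stated comparison of the primary outcome uses follow-up periods only and leaves baseline to further analyses

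*Protocol article*

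**What the plan says.** The Design section describes the study as "comparing changes in screening and brief advice, and, if relevant, referral for treatment activity, amongst primary health care units (PHCUs) in intervention cities" with those in similar control cities. The contrast named there is one of change.

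The Statistical measures section then fixes three things:

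- The primary outcome is "measured during two four-week periods midway and at the end of the 18-month scale-up period". Baseline is not one of these periods.
- Because the event is rare, "we will use exact inference methods for comparison of intervention vs. control cities". No baseline term is attached to this comparison.
- Covariates come in at the next step: "For further analyses, including covariates, regression models will be used". These models respect the hierarchy of the data and include PHCU and city characteristics, "incorporating 4-week baseline period measurements as covariates".

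The Abstract announces a ratio with its confidence interval "of the proportion of patients receiving intervention in the implementation cities with the proportions in the comparator cities", again without a baseline term, although it also lists baseline among the formal evaluation points.

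The Cities section states that intervention and comparator municipalities were selected by the investigators. The Discussion describes the design as "trying to optimize control for confounding, and using propensity score matching (PSM), given the above constraints". Propensity score matching does not appear in the Statistical measures section.

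**The concern.** In a randomised trial a follow-up-only comparison is unbiased, and baseline adjustment mainly adds precision. Here there is no randomisation. If PHCUs in the intervention municipalities already screened and advised more (or less) than those in the comparator municipalities, a follow-up ratio combines that earlier difference with the effect of the programme.

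The Data collection section already provides a four-week baseline. It is the most direct protection against this confounding, because it measures the outcome itself. The plan collects it and intends to use it, but not in the comparison it sets out for the primary outcome. The document therefore offers two different contrasts for the headline result. Someone working from it could take either as primary after seeing the data.

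**Working it through.** **Inputs from the plan.** The Sample size section gives a baseline rate of 2.5 per 1,000, a target of 5 per 1,000, 30 PHCUs per group, 1,200 adult consultations per PHCU per month and an ICC of 0.03. The target ratio is 5/2.5 = 2.0. The plan gives no figure for comparability at baseline and no correlation between baseline and follow-up, so both are assumed below over a range. The point does not rest on the sample size.

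**Step 1: what each contrast estimates.** Let b_I and b_C be the true baseline rates and θ the true multiplicative effect, with any time trend common to both groups.

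- Follow-up ratio = θ × b_I / b_C
- Ratio of follow-up-to-baseline ratios = θ

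The follow-up ratio is off by the factor b_I / b_C. With b_C = 2.5 per 1,000 and b_I assumed:

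| True effect | b_I per 1,000 | Follow-up ratio | Ratio of follow-up-to-baseline ratios |
|---|---|---|---|
| None | 3.0 | 1.2 | 1.0 |
| None | 3.75 | 1.5 | 1.0 |
| None | 5.0 | 2.0 | 1.0 |
| Doubling | 1.25 | 1.0 | 2.0 |
| Doubling | 3.75 | 3.0 | 2.0 |

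A twofold difference at baseline would by itself equal the whole target effect. In the other direction it would hide a true doubling.

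**Step 2: chance of a significant result with no effect, baselines 3.75 v 2.5 per 1,000.** Normal approximation, two-sided 5%, one four-week period.

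- Consultations treated as independent: n = 30 × 1,200 = 36,000 per group. The standard error of the difference is √(2 × 0.003125 × 0.996875 / 36,000) = 0.000416. The difference is 0.00125 and the critical value 1.96 × 0.000416 = 0.000815. Then (0.00125 − 0.000815)/0.000416 = 1.04, a rejection probability of about 85%.
- At the plan's ICC: design effect 1 + 1,199 × 0.03 = 36.97, effective n = 36,000/36.97 = 974. The rejection probability is about 8%.

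The distortion of the ratio is the same in both cases. Only the width of the interval differs.

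**Step 3: precision.** Take equal variances at both times and a PHCU-level correlation r (assumed). Variance relative to follow-up only is 2(1 − r) for a pure change contrast and 1 − r² for covariate adjustment.

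| r | Change contrast | Baseline as covariate |
|---|---|---|
| 0.3 | 1.40 | 0.91 |
| 0.5 | 1.00 | 0.75 |
| 0.7 | 0.60 | 0.51 |

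The change contrast loses precision when r is below 0.5. Covariate adjustment does not lose precision at any r in this approximation.

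**Step 4: a limit of covariate adjustment.** Under the same assumptions the regression slope is r, so a lasting baseline difference is removed only in the proportion r. For a difference of 3.75 − 2.5 = 1.25 per 1,000 and r = 0.5, 1.25 × (1 − 0.5) = 0.625 per 1,000 remains. This matters because one baseline month yields about 1,200 × 0.0025 = 3 expected events per PHCU, which makes the covariate noisy.

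**The case against.** **The rank of the analyses is inferred.** The word primary is attached to the outcome, not to an analysis, and the regressions are never called secondary. The sentence on odds ratios follows the modelling sentences, so the reported estimate may be the adjusted one. A model with baseline as covariate is also a recognised way to compare groups on change, and an analysis plan that is not shown may settle the order. It stands that baseline adjustment is planned in advance. A reader might infer that the study ignores baseline, and the document does not support that. But the one comparison stated for the primary outcome has no baseline term, the regressions are introduced as additional, and the Abstract's ratio follows the unadjusted form. The conflict with the Design section remains.

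**Comparators were chosen to be comparable.** The Cities section names socio-economic and other characteristics bearing on drinking, health care and survival, and community mental health services. This may reduce imbalance. Prior screening and advice activity is not among the listed criteria. Intervention municipalities also had to give technical and political consent, which could go with greater readiness.

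**No systematic imbalance is shown.** This is correct. A reader might point to the chance spread of the baseline difference at the plan's ICC, √(2 × 0.0025 × 0.9975 × 36.97/36,000) = 2.3 per 1,000, as evidence of bias. It is not. It is random variation between sets of PHCUs, which an interval that allows for clustering would cover.

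**Propensity score matching is a further safeguard.** A reader might infer that three municipalities are to be matched with three and dismiss the idea. The Discussion names no unit, and matching PHCUs or providers is possible. What stands is only that the method is claimed in the Discussion and has no place in the stated analysis.

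**Conclusion.** The point holds as an inconsistency with consequences for the headline estimate. The Design section promises a comparison of changes, while the stated comparison of the primary outcome and the Abstract's ratio use follow-up alone, with baseline adjustment left to further analyses.

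Followed as written, the estimate is multiplied by the ratio of the groups' underlying baseline rates. For assumed intervention baselines of 3.0 to 5.0 per 1,000 against 2.5, that factor is 1.2 to 2.0. These values are illustrations. The conclusion is that an earlier difference can enter the result, not that it will, and the document gives no basis for predicting its direction or size. The arithmetic also assumes a common time trend in both groups.

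The bias argument does not depend on the baseline-follow-up correlation. Any gain in precision does.

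**What to change.** - In Statistical measures, name as primary the regression already planned, with the PHCU's baseline rate as covariate, clustering accounted for and country as stratum. Covariate adjustment is preferable to a pure change contrast on precision, given that the correlation is unknown.
- Report the unadjusted follow-up ratio as descriptive. Give the ratio of follow-up-to-baseline ratios as a supporting estimate, since the covariate model may leave part of a baseline difference in place.
- Align the Abstract and the Design section with this contrast.
- Either carry the propensity score matching from the Discussion into Statistical measures as a PHCU-level sensitivity analysis or remove it.

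**Cost.** No new data are needed, as the baseline period is already planned. There is slightly more modelling with a rare outcome. The precision of the adjusted analysis cannot be stated until a baseline-follow-up correlation is assumed, so the power statement should be checked over a range of values. The change should be made before follow-up data are seen.
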